### Data management

Data will be recorded in a web-based data capture system (OpenClinica), which is hosted by the Primary Care Clinical Trials Unit of the University of Oxford. This system is customised and has an audit trail facility. Ranges and programmed validation checks are implemented in the system in order to aid reliable data entry.

### Statistical analysis

The primary and secondary outcomes will be assessed using an intention-to-treat analysis by an independent statistician. Each continuous outcome will be assumed to follow the normal distribution and be analysed by means of a linear mixed-effects model, adjusted for outcome at baseline. The model will include fixed-effects terms for randomised group, visit, interaction between randomised group and visit, and baseline BMI (for non-weight outcomes only), and random effects to account for repeated measures on the same participant at 3, 6 and 12 months. No adjustment will be made for baseline BMI in the analysis of the weight outcomes due to its strong collinearity with baseline weight. A random effect will also be included for individual practice. An unstructured variance–covariance matrix will be specified between repeated measurements on the same individual, and the random effects for patient and practice will be assumed to be independent. The adjusted treatment effect together with the 95% CI and p value will be reported. The analysis will be performed using PROC MIXED in SAS Version 9.4. The proportion of participants who lose 5% and 10% of their initial weight at 12 months, respectively, will be presented, and the adjusted difference between the two arms and 95% CI will be reported. The binary outcome will be analysed by means of a logistic mixed-effects model, adjusting for baseline BMI (fixed effect) and practice (random effect). The number needed to treat to achieve 5% or 10% weight loss, defined as the inverse of the absolute difference in proportions, will be reported if the differences between the treatment and control groups are statistically significant. A full statistical analysis plan will be prepared prior to any data analysis.

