### Sample size

The total number of participants to be recruited for this study is 270. This is based on a sample size calculation for the primary outcome using equal variance independent samples t-test assuming a difference between groups at 12 months of 4 kg with an SD in both groups of 9 kg, obtained from a meta-analysis of published studies.^11^ The sample size has been inflated by 20% to account for attrition, and assumes 90% power and two-sided alpha of 5%.

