### Randomisation

All eligible, consenting participants will be randomised with an allocation ratio of 1:1 to low-energy total diet replacement or usual care programmes using an online programme, which reveals group allocation as per a computer-generated randomisation list. The randomisation criteria will be validated by an independent statistician. Allocation will be stratified by GP practice and baseline BMI (≤35 kg/m^2^ or >35 kg/m^2^) using stratified block randomisation with randomly varying block sizes of 2, 4 and 6. The randomisation software ensures full allocation concealment, with the allocation group only revealed to the person performing the randomisation once a study identifier and required stratification details have been entered.

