#### Sociodemographic characteristics

Participants will be asked to self-report age, sex and ethnicity.

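### The stated weight model adjusts for baseline weight alone, with no baseline-by-visit term and without age or sex, so some precision on the 12-month contrast may be forgone

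*Protocol article*

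**What the plan says.** The Statistical analysis section of the protocol article describes one linear mixed model for the continuous outcomes, adjusted for the outcome's baseline value. Its terms are given as: "The model will include fixed-effects terms for randomised group, visit, interaction between randomised group and visit, and baseline BMI (for non-weight outcomes only"). Practice enters as a random effect, and the within-person covariance over 3, 6 and 12 months is unstructured. Baseline BMI is left out of the weight models, and the reason given is collinearity with baseline weight. The section ends by saying that a full SAP will be prepared before analysis.

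Under Sociodemographic characteristics: "Participants will be asked to self-report age, sex and ethnicity". Neither age nor sex appears in the description of the model.

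The Sample size section names its method thus: "sample size calculation for the primary outcome using equal variance independent samples t-test". Its planning values are a 4 kg difference and a common SD of 9 kg, so no covariates are used.

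**The concern.** Two kinds of prognostic information may go unused.

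**Baseline slope.** The model lets the treatment effect and the residual variance differ by visit, but no term lets the slope on baseline weight differ. The visits fall at different stages. The 3-month visit follows total diet replacement and food reintroduction, the 6-month visit follows the maintenance phase, and the 12-month visit comes about six months after free provision ends. The article itself expects regain. It is plausible, though not documented, that the relation of weight change to baseline weight shifts over that course. With unstructured covariance, a common slope is driven mainly by the less variable visits. If variability grows with time, 12 months is not among them.

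**Age and sex.** Both are recorded. If they predict weight change at a given baseline weight, adjusting for them narrows the confidence interval without new data.

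At stake is the width of the interval for the primary contrast and, to a lesser extent, for the secondary continuous outcomes. Its validity is not in question.

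**Working it through.** **1. The plan's own figure.** Inputs from the Sample size and Randomisation sections: difference 4 kg, SD 9 kg, 90% power, two-sided 5%, 1:1 allocation, 20% attrition. A two-sample t-test with d = 4/9 needs 107.36, so 108 per arm and 216 in total. Then 216/(1 − 0.20) = 270, which matches exactly. With 108 per arm the power is 90.2% (noncentral t) or 90.4% (normal approximation). The standard error is 9 × √(2/108) = 1.22 kg, and the 95% half-width is 1.96 × 1.225 = 2.40 kg.

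**2. Adding age and sex.** Assumption: 9 kg is the residual SD before they are added, and they explain a share R² of that variance. The residual SD becomes 9√(1 − R²). Estimating two more coefficients multiplies the variance by about 1 + 2/210. Power is noncentral t at 108 per arm, without and with that charge:

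| Assumed R² | Power, no charge | Power, net of charge | Net 95% half-width |
|---|---|---|---|
| not added | 90.2% | – | 2.40 kg |
| 0% | 90.2% | 89.9% | 2.41 kg |
| 1% | 90.5% | 90.2% | 2.40 kg |
| 2% | 90.7% | 90.5% | 2.39 kg |
| 5% | 91.6% | 91.3% | 2.35 kg |
| 10% | 92.9% | 92.7% | 2.29 kg |

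The gain at 2% is 0.3 points net, or 0.6 without the charge. At 10% it is 2.5 points net, or 2.7 without. Break-even is where (1 − R²)(1 + 2/210) = 1, that is R² = 0.9%. With no prognostic value at all, about 0.3 points are lost.

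**3. Letting the baseline slope vary by visit.** Assumptions, none of them in the article: residual SDs 5, 7 and 9 kg at 3, 6 and 12 months; correlations 0.8 (3 with 6), 0.6 (3 with 12) and 0.8 (6 with 12); baseline-weight SD 15–25 kg. If the true slopes of weight change on baseline are the vector b and the residual covariance is V, the common slope settles at b_c = (1′V⁻¹b)/(1′V⁻¹1). The 12-month variance is inflated by the factor 1 + [(b₁₂ − b_c) × SD_baseline]²/81.

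Worked case: slopes −0.15/−0.12/−0.05 give b_c = −0.152. At a baseline SD of 20 kg the factor is 1 + (0.102 × 20)²/81 = 1.05.

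| Assumed slopes at 3/6/12 months | Inflation of 12-month variance (baseline SD 15–25 kg) | Power (normal approximation, against 90.4%) |
|---|---|---|
| equal | 0% | 90.4% |
| −0.10/−0.09/−0.07 | 0.3–0.7% | 90.2–90.3% |
| −0.12/−0.10/−0.06 | 1–3% | 89.6–90.1% |
| −0.15/−0.12/−0.05 | 3–8% | 88.2–89.6% |
| −0.20/−0.15/−0.05 (extreme) | 7–18% | 85.2–88.6% |

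The power column takes 9 kg as the residual SD when slopes are visit-specific.

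A simulation with 216 completers and 1,500 runs, at a baseline SD of 20 kg, gave variance ratios (common over visit-specific) of 1.00 for equal slopes. For the last three slope sets the ratios were 1.02, 1.07 and 1.11. A separate simulation with 21–22% dropout related to earlier weight showed no meaningful bias from the common slope.

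**The case against.** The strongest reply is that the article does not fix these details. The quoted list does not itself contain the baseline outcome, which stands in the sentence before it, so the list is not exhaustive. The single slope is inferred from the absence of an interaction. The article also defers to a full SAP, and the Trial Steering Committee section says that committee has reviewed one. In addition, age and sex are not stratification factors, a short covariate set is a legitimate choice, and every figure for the gain is assumed.

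Much of this stands. It would be wrong to call the model fully specified, and the SAP may already hold the missing terms. Still, the section names the fixed and random effects, the covariance structure and the software, and it justifies one exclusion. The covariate set is stated rather than left open, so it is fair to suggest an improvement to it.

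A reader might infer more than the text supports:

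- **That every continuous outcome is adjusted for its baseline value only.** Non-weight outcomes also adjust for baseline BMI; the description fits weight alone.
- **That precision is lost for certain.** Nothing in the article gives an R² or slopes by visit. If R² is below about 1% and the slopes are equal, nothing is gained by the change.
- **That the estimate is biased or the sample size wrong.** Randomisation protects the planned contrast, and 270 follows from an unadjusted t-test.
- **That all secondary outcomes need the interaction.** HbA1c and LDL cholesterol are listed at 12 months only, so there are no separate visit slopes to fit.

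**Conclusion.** The point holds as an efficiency suggestion. For weight, the stated model carries one baseline covariate, lists no baseline-by-visit term and leaves out two recorded variables that may be prognostic. The possible gain is modest: about 0.3 to 2.7 power points if age and sex explain 2–10% of residual variance, and 0 to about 8% of the 12-month variance over plausible differences in slope. Only a deliberately extreme slope set reaches 18%. These ranges depend on the assumed R², visit SDs, correlations, baseline-weight SD and slopes. Neither the validity of the planned analysis nor the derivation of 270 is in doubt. If the SAP already contains these terms, nothing remains to be done.

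**What to change.** In the analysis plan, before any by-arm data are seen:

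1. Add the interaction of the outcome's baseline value with visit for continuous outcomes analysed at several visits: weight, and fat mass and blood pressure where they are modelled repeatedly.
2. Add age and sex as fixed effects in the continuous-outcome models.
3. Keep the model as now written as a sensitivity analysis.

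The cost is about one sentence and, for weight, four more parameters (two for the interaction over three visits, one each for age and sex). No new data are needed. The downside is the small loss shown above if the covariates prove uninformative. Timing matters, because covariates chosen after by-arm results are known would look selective.

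### The weight models omit the BMI randomisation stratum on a collinearity argument that does not apply to the treatment effect; the cost is small and conservative, and the remedy is nearly free

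*Protocol article*

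**What the plan says.** Under Randomisation, the protocol article states: "Allocation will be stratified by GP practice and baseline BMI", with BMI split at 35 kg/m². Participants are "randomised with an allocation ratio of 1:1", "using stratified block randomisation with randomly varying block sizes of 2, 4 and 6".

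Under Statistical analysis, each continuous outcome is "analysed by means of a linear mixed-effects model, adjusted for outcome at baseline", so the weight models carry baseline weight. The first stratification factor is also kept: "A random effect will also be included for individual practice". BMI appears in the list of fixed effects only for outcomes other than weight, and the exclusion is then explained: "No adjustment will be made for baseline BMI in the analysis of the weight outcomes due to its strong collinearity with baseline weight". The weight models therefore contain no BMI term in any form, whether continuous or as the two-level stratum. This covers the primary outcome and the weight changes at 3 and 6 months.

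The proportions losing 5% and 10% of weight are handled differently, by a "logistic mixed-effects model, adjusting for baseline BMI (fixed effect) and practice (random effect"). No baseline weight is listed for that model.

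**The concern.** When allocation is balanced within strata, part of the variation in outcome between strata can no longer contribute to chance differences between the arms. An analysis that ignores the strata still counts that variation as residual error. The estimate stays unbiased, but its reported standard error is too large to the extent that the stratum predicts the outcome given the other terms in the model. Analysing by the factors used in randomisation avoids this.

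Here one of the two factors is left out of the primary model, by an explicit rule with a stated reason, so this is not a detail left to the analysis plan. The reason would matter if the BMI or weight coefficient were of interest. It has no force for a randomised comparison, because treatment is independent of both covariates and is balanced over BMI by design. What is at stake is a little precision and power in the primary analysis, and an incorrect justification on the record.

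**Working it through.** **1. The plan's own figure.** Inputs from the Sample size section: difference 4 kg, SD 9 kg, 90% power, two-sided 5%, 20% attrition, equal-variance t-test. The noncentral t calculation gives 108 per arm, 216 in total, and 216 / (1 − 0.20) = 270. The stated total reproduces exactly.

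**2. Does collinearity harm the treatment effect?** The variance inflation factor of a coefficient is 1 / (1 − R²), where R² comes from regressing that covariate on the others in the model. The documents give no joint distribution of weight, height and BMI, so one was assumed: BMI as 30 plus a gamma variable (shape 2.2, scale 3.2), height with mean 1.67 m and SD 0.09 m, giving a weight–BMI correlation of 0.76. Trials of 216 participants in 10 practices were simulated with permuted blocks of 2, 4 and 6 within practice and BMI stratum, 4,000 per scenario. Average inflation factors:

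- weight with continuous BMI: 2.4
- weight with the two-level stratum: 1.4
- treatment, with weight and continuous BMI both in the model: 1.007

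The covariates are collinear, as the article says, but the treatment coefficient is practically untouched. When the stratum has no effect beyond weight, adding it moves the mean treatment standard error from 1.226 to 1.227 kg (0.001 / 1.226, about 0.1%).

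**3. What could inclusion gain?** Take 9 kg as the residual SD without the stratum. With 108 per arm, SE = 9 × √(2/108) = 1.225 kg. If the stratum explains a share r of the remaining variance, the SE becomes 1.225 × √(1 − r). Power at 4 kg by the normal approximation is Φ(4/SE − 1.96). The true size of the test that omits the stratum, if balance were perfect, is 2 × [1 − Φ(1.96 / √(1 − r))].

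| Assumed partial R² (r) | SE with stratum (kg) | Change in SE | Power | Size of test without stratum |
|---|---|---|---|---|
| 0 | 1.225 | 0 | 90.4% | 5.0% |
| 2% | 1.212 | −1.0% | 91.0% | 4.8% |
| 5% | 1.194 | −2.5% | 91.8% | 4.4% |
| 10% | 1.162 | −5.1% | 93.1% | 3.9% |

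(The noncentral t puts the first power at 90.2%.)

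**4. Check by simulation.** This used the trials from step 2, with 12-month weight regressed on treatment and baseline weight, with or without the stratum, and residual SD 9 kg after the stratum. The stratum effect is the difference in 12-month weight between strata at equal baseline weight.

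| Stratum effect | Mean SE without / with (kg) | Type I error without / with |
|---|---|---|
| 0 | 1.226 / 1.227 | 5.2% / 5.2% |
| 2 kg | 1.230 / 1.225 | 4.7% / 4.8% |
| 4 kg | 1.245 / 1.226 | 4.8% / 4.9% |
| 6 kg | 1.270 / 1.225 | 4.5% / 5.1% |

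The ratio of squared SEs shows where these cases sit in the first table: 1 − (1.226/1.245)² is about 3% for 4 kg, and 1 − (1.225/1.270)² about 7% for 6 kg. With a true treatment difference of 4 kg, power without and with the stratum was 89.9% and 90.1% (2 kg stratum effect), and 89.8% and 90.6% (4 kg). Mean error of the treatment estimate was below 0.05 kg throughout. With 4,000 runs the simulation error of a 5% rejection rate is √(0.05 × 0.95 / 4000), about 0.3 points, so small type I differences are not distinguishable.

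**The case against.** The best defence is that baseline weight is already in the model and carries much of the BMI information. At a given weight, BMI differs only through height, and nothing in the article suggests that height explains 5 or 10% of the residual variation in 12-month weight. The gain could be nil. This stands: the gain is conditional on an undocumented quantity, and a reader who infers that the plan certainly discards precision goes further than the documents allow.

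A reader might also infer that the plan contradicts itself by adjusting for BMI elsewhere. The 5% and 10% models are weak evidence for that, because they list no baseline weight, so no collinearity arises there. The rule can be read as using BMI where baseline weight is absent. What remains is that BMI is kept for fat mass, a secondary outcome adjusted for its own baseline, which can be expected to track BMI too. The same would apply to waist circumference if the exploratory outcomes use this model. The collinearity reason is thus not applied evenly, but no two passages conflict.

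Third, the calculations are a single-time-point regression without a practice effect, whereas the plan specifies a repeated-measures mixed model. The sizes are therefore indicative. The argument about collinearity does not depend on them.

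**Conclusion.** The rationale is wrong for the treatment effect, and one of the two stratification factors is missing from the weight models because of it. The consequence runs in one direction only: a standard error that is equal or slightly too large, and a test at or slightly below its nominal size. Over assumed partial R² values from 0 to 10%, including the stratum would raise power from about 90.4% to between 90.4% and 93.1%. In the simulations, a 4 kg difference between strata at equal baseline weight was worth just under one point.

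It would be tempting to read the omission as undermining the primary analysis, through bias, an inflated false-positive rate or an inadequate sample size. The documents do not support that. The estimate is unbiased, the error is conservative, practice is already modelled, and 270 follows exactly from the stated inputs. These sizes rest on assumed BMI and height distributions, a residual SD of 9 kg and the assumed partial R². The point is minor, but the change is nearly free.

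**What to change.** In the Statistical analysis section, replace the sentence excluding BMI with: *The weight models will also include the randomisation stratum (BMI ≤35 / >35 kg/m²) as a fixed effect, in addition to baseline weight and the practice random effect.* Delete the collinearity rationale. Leave the covariates of the other models as they are; nothing here argues for adding baseline weight to them.

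The cost is one sentence and one degree of freedom. The stratum is already recorded for randomisation. If it adds nothing beyond baseline weight, the standard error rises by about 0.1%. The article says that the full analysis plan will be written before any data are analysed, so the change can be prespecified there. The sample size needs no revision.

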### Qualitative substudy

The purpose of this study is to examine participants’ views of the programmes. In particular, we aim to examine the features that helped or hindered adherence to the programme and participants’ views of the behavioural support provided in the respective programmes. We will therefore purposively sample participants based on their responses to the satisfaction questionnaire, reflecting positive, neutral and negative evaluations. Where possible, we will select participants to reflect both genders, socioeconomic status and ethnic group differences. We anticipate interviewing around 20 participants in the intervention group and 10 in the control group, but sampling will continue until saturation is reached, evidenced by no new themes occurring.

We will develop a semistructured topic guide for the interviews. The interviewer will encourage respondents to discuss their perceptions and experiences freely and in depth. The interview will set the context by asking about previous experience of weight management. Thereafter, we will ask for participants’ views on which component parts of their treatment they felt were effective and which they felt were not effective; thoughts about ability to continue to manage their weight when treatment has ended; and their views on medication adjustments where these occurred. The acceptability of the weight management treatment programmes and any preference they initially had for the total diet replacement programme or the usual care programme will be explored.

Data from participants will be collected in a confidential, telephone interview, which will be audio-recorded. All interviews will be transcribed. To examine saturation, analysis will proceed concurrently with interviewing.

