**Methods and analysis:**

The DROPLET trial is a randomised controlled trial comparing a low-energy total diet replacement programme with usual weight management interventions delivered in primary care. Eligible patients will be recruited through primary care registers and randomised to receive a behavioural support programme delivered by their practice nurse or a referral to a commercial provider offering an initial 810 kcal/d low-energy total diet replacement programme for 8 weeks, followed by gradual food reintroduction, along with weekly behavioural support for 24 weeks. The primary outcome is weight change at 12 months. The secondary outcomes are weight change at 3 and 6 months, the proportion of participants achieving 5% and 10% weight loss at 12 months, and change in fat mass, haemoglobin A1c, low-density lipoprotein cholesterol and systolic and diastolic blood pressure at 12 months. Data will be analysed on the basis of intention to treat. Qualitative interviews on a subsample of patients and healthcare providers will assess their experiences of the weight loss programmes and identify factors affecting acceptability and adherence.

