#### Questionnaires

Participants will be provided with a questionnaire booklet which they will be asked to complete and return to the trial team in a postage paid envelope provided. The questionnaire booklet contains the following measures:
*OWLQOL*: a weight-specific instrument intended to be used to assess obesity-specific symptoms and quality of life, general functional status and well-being, and person-specific preference measurement.^21^

*Quality of life*: EQ-5D will be used as a standardised validated instrument used for measuring general health status.^22^

*Programme adherence*: self-reported adherence to the allocated programme and methods participants are using to attempt to lose weight will be recorded by questionnaire.
*Programme feedback*: will be assessed using several 5-point Likert scales, including whether there is an aim to continue with the programme.
*OxFAB*: a questionnaire to assess personal strategies used by individuals for the purposes of weight loss.^18^

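### Interviewees are chosen on satisfaction-questionnaire responses, so people who stop or never start and do not return the form have no stated route into interviews about what hindered adherence

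*Protocol article*

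**What the plan says.** The Qualitative substudy section gives its particular aim as: "we aim to examine the features that helped or hindered adherence to the programme". It then states the selection rule: "We will therefore purposively sample participants based on their responses to the satisfaction questionnaire", "reflecting positive, neutral and negative evaluations". The other criteria are demographic: "Where possible, we will select participants to reflect both genders, socioeconomic status and ethnic group differences". On numbers it says "We anticipate interviewing around 20 participants in the intervention group and 10 in the control group", with recruitment continuing until interviews yield no fresh themes.

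The Questionnaires section describes a booklet "which they will be asked to complete and return to the trial team in a postage paid envelope provided". The booklet holds both the programme-feedback scales, which include an item on intention to carry on, and self-reported adherence.

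Three other sections bear on the point. Exploratory outcomes lists the interviews (at 6 and 12 months) and, separately, the proportion still trying to lose weight and following the programme at 4, 8 and 12 weeks. Retention and withdrawal keeps everyone in follow-up except those who expressly withdraw from the study, and offers a gift card for attending the 6- and 12-month visits. The abstract describes "Qualitative interviews on a subsample of patients and healthcare providers".

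**The concern.** The frame and the aim do not match well. People who found the programme too hard, or never began it, are among those best placed to say what hindered adherence. They may also be less likely to post back a booklet about it. Someone without a questionnaire response has nothing on which to be selected under the stated rule, and the article gives no second route.

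Satisfaction is also not the same as adherence. A satisfied person may stop for practical reasons, and a dissatisfied person may finish. Sampling across positive, neutral and negative views therefore does not ensure a spread across starting, stopping and completing.

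Continuing to saturation does not repair this, because the absence of fresh themes is judged only among people the frame can reach. Acceptability is part of the trial's stated objective, and the abstract says the interviews will identify factors affecting acceptability and adherence. Views that were never sought cannot be recovered at analysis.

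**Working it through.** **The rule set against the aim**

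1. Aim: features that helped or hindered adherence (Qualitative substudy).
2. Selection variables: satisfaction response; where possible gender, socioeconomic status and ethnic group (same section).
3. Not among them: having started, having stopped, having completed, or not having returned the form.
4. Source of the satisfaction response: the Questionnaires section does not use the term satisfaction questionnaire. The programme-feedback scales are the only instrument described that fits. Equating the two is an inference.
5. Mode: completed and posted back by the participant. The gift card rewards attending visits, not returning the booklet.
6. Follow-up of people who stop: they are asked back so that outcomes can be measured. This is not linked to interview selection.

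From 2 to 6, a stopper who returns the form can be chosen, and a stopper who does not has no stated route.

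**The number per arm**

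The plan's total of 270 reproduces. A two-sample t-test with difference 4 kg, SD 9 kg, two-sided alpha 5% and power 90% needs 107.36, so 108 per arm. Then 2 × 108 / (1 − 0.20) = 270. With 1:1 allocation that is 135 per arm. The point does not depend on this figure; it only scales the illustration.

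**Illustration under assumptions**

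- Proportion who stop, s = 0.36. This is the complement of the 64% completion in the observational report cited in the Introduction (n=91, with completion defined as 12 weeks or 20 kg lost). It is not an estimate for this trial.
- Return rate among continuers, r_c = 0.80 to 0.90 (assumed).
- Return rate among stoppers, r_s = 0.80 down to 0.20 (assumed).

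Stoppers in the arm: 135 × 0.36 = 48.6.
Stoppers outside the frame: 48.6 × (1 − r_s).
Stoppers' share of the frame: s·r_s / [s·r_s + (1 − s)·r_c].

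| r_s | Stoppers outside frame | Stoppers in frame | Share of frame (r_c = 0.90 to 0.80) |
|---|---|---|---|
| 0.80 | 9.7 | 38.9 | 33% to 36% |
| 0.60 | 19.4 | 29.2 | 27% to 30% |
| 0.40 | 29.2 | 19.4 | 20% to 22% |
| 0.20 | 38.9 | 9.7 | 11% to 12% |

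If only 20% stopped (also an assumption), there would be 135 × 0.20 = 27 stoppers. The same four return rates would leave 5.4, 10.8, 16.2 and 21.6 of them outside the frame.

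Two things follow. When stoppers and continuers return the form equally often, the stoppers' share stays at 36%, although those who do not return it are still left out. Even at the lowest return rate shown with s = 0.36, about 10 stoppers remain available. The exposure is therefore partial, and it turns on a return rate that the article does not give.

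**The case against.** The best case for the plan is that the loss is narrower than it first looks.

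- **The instrument.** The link between the satisfaction questionnaire and the posted booklet is inferred. The schedule figure is not shown, and continuation is assessed as early as 4 weeks, so some early stoppers may have responded before they stopped. This stands, and it is why the point is confined to what the article states.
- **Existing safeguards.** Negative views are deliberately sought, the feedback scales carry an intention-to-continue item, and people who stop remain in follow-up. These help with stoppers who respond. They do not open a route for those who do not.
- **Condensed article.** Handling of non-responders might be in the full protocol. But the article states a selection rule, and it is that rule which leaves programme status out.
- **Weight.** The interviews are exploratory, and choosing satisfaction as the main axis is defensible. This stands and keeps the point small.

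A reader might infer several stronger claims that the documents do not support:

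- **That people who stop cannot be interviewed at all.** Those who return the form can be.
- **That acceptability would be overstated.** Purposive interviews seek a range of views and do not estimate how common acceptance is, and no return rate is known.
- **That saturation should be declared separately for people who stopped.** That could not be assured with about 20 intervention interviews.
- **That the provider interviews will yield no data.** The abstract and the Introduction mention healthcare providers or practitioners, whereas Exploratory outcomes and Qualitative substudy speak only of participants. The full protocol may settle this, so it is at most wording to reconcile.

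**Conclusion.** The point holds in a limited form: the stated selection rule fits only part of the substudy's own aim. Programme status is not a criterion, and those who stop or never start and do not return the form have no stated route to interview. Barriers to adherence may be under-represented as a result. This is a plausible risk whose size cannot be derived from the article. The illustrative counts rest on a borrowed 36% and on assumed return rates.

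The conclusion also rests on reading the satisfaction questionnaire as the booklet's feedback scales. If it is collected another way, such as at a visit, the point shifts to people who miss that contact, but the absence of programme status as a criterion remains. No primary, secondary or safety result is touched. It is an inexpensive improvement to an exploratory component.

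**What to change.** Keep the planned numbers of about 20 and 10, and change the sampling paragraph of the Qualitative substudy section in three ways.

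1. Add programme status (not started, stopped early, completed) as a purposive criterion alongside satisfaction. Take it from the 4-, 8- and 12-week continuation data or from counsellor or nurse contacts. If the continuation data come through the same posted booklet, the contacts are the source that would cover non-returners.
2. Allow direct invitation of people who did not return the questionnaire and have not withdrawn from the study.
3. Report interviewees by programme status, so that readers can see whose views informed the judgement of saturation.

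While editing, align the abstract and the Introduction with Exploratory outcomes and Qualitative substudy on whether healthcare providers are interviewed.

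The cost is a wording change and some extra effort to reach people who stopped. The article does not say whether counsellor or nurse contact records reach the trial team, so a way to obtain them may have to be arranged. The change has to be made before interviewing ends.
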